## 7.4 Planned Outcome Tables

| **Table 5.** Cox regression models for Primary and Secondary Time-to-Event endpoints.(ITT population) | | | | | | |
| --- | --- | --- | --- | --- | --- | --- |
| **Outcome** | **Adjusted for Site and Device type** | | | **Adjusted for Site and Device type, Age, Gender and NYHC** | | |
|  | **Hazard Ratio^✝^** | **95% CI** | **P value** | **Hazard Ratio^✝^** | **95% CI** | **P value** |
| **Death or first unplanned hospitalisation for CV reasons (Primary)** | X.XX | X.XX to X.XX | X.XXX | X.XX | X.XX to X.XX | X.XXX |
| **All cause mortality^*^** | X.XX | X.XX to X.XX | X.XXX | X.XX | X.XX to X.XX | X.XXX |
| **CV related mortality^*^** | X.XX | X.XX to X.XX | X.XXX | X.XX | X.XX to X.XX | X.XXX |
| **Non-CV related mortality** | X.XX | X.XX to X.XX | X.XXX | X.XX | X.XX to X.XX | X.XXX |
| **CV related death or first unplanned hospitalisation for CV reasons** | X.XX | X.XX to X.XX | X.XXX | X.XX | X.XX to X.XX | X.XXX |
| **Death or first unplanned hospitalisation for non-CV reasons** | X.XX | X.XX to X.XX | X.XXX | X.XX | X.XX to X.XX | X.XXX |
| **First unplanned hospitalisation for CV reasons** | X.XX | X.XX to X.XX | X.XXX | X.XX | X.XX to X.XX | X.XXX |
| **First unplanned hospitalisation for non-CV reasons** | X.XX | X.XX to X.XX | X.XXX | X.XX | X.XX to X.XX | X.XXX |

✝ Hazard ratio calculated with the UCP group set as the reference.

* Sensitivity analyses and listings will be performed around ACM and CV mortality including (and not including) CV death equivalents (heart transplantation, appropriate shock from ICD, LTAD insertion and survived resuscitation of sudden cardiac arrest)

| **Table 6.** Poisson regression models for secondary count outcomes (follow-up time included as an offset). (ITT population) | | | | | | |
| --- | --- | --- | --- | --- | --- | --- |
| **Outcome** | **Adjusted for Site and Device type** | | | **Adjusted for Site, Device type, Age, Gender and NYHC** | | |
|  | **Relative Risk^✝^** | **95% CI** | **P value** | **Relative Risk^✝^** | **95% CI** | **P value** |
| **Total number of unplanned hospitalisations** | X.XX | X.XX to X.XX | X.XXX | X.XX | X.XX to X.XX | X.XXX |
| **All cause mortality** | X.XX | X.XX to X.XX | X.XXX | X.XX | X.XX to X.XX | X.XXX |

✝ Relative risk calculated with the UCP group set as the reference.

| **Table 7a.** Quality of Life Endpoints at 2 years. (ITT population) | | | | | | | |
| --- | --- | --- | --- | --- | --- | --- | --- |
| **Outcome** | | **Adjusted for Site, Device type and Baseline score** | | | **Adjusted for Site, Device type, Age, Gender, NYHC and Baseline score** | | |
|  |  | **Difference^✝^** | **95% CI** | **P value** | **Difference^✝^** | **95% CI** | **P value** |
| **EQ-5D** | Visual Analogue | XX.XX | XX.XX to XX.XX | X.XXX | XX.XX | XX.XX to XX.XX | X.XXX |
|  | Total | XX.XX | XX.XX to XX.XX | X.XXX | XX.XX | XX.XX to XX.XX | X.XXX |
| **SF-12** | Physical Component Summary (PCS) | XX.XX | XX.XX to XX.XX | X.XXX | XX.XX | XX.XX to XX.XX | X.XXX |
|  | Mental Component Summary (MCS) | XX.XX | XX.XX to XX.XX | X.XXX | XX.XX | XX.XX to XX.XX | X.XXX |
|  | Total | XX.XX | XX.XX to XX.XX | X.XXX | XX.XX | XX.XX to XX.XX | X.XXX |
| **KCCQ** | Physical Limitation | XX.XX | XX.XX to XX.XX | X.XXX | XX.XX | XX.XX to XX.XX | X.XXX |
|  | Symptom Frequency | XX.XX | XX.XX to XX.XX | X.XXX | XX.XX | XX.XX to XX.XX | X.XXX |
|  | Symptom burden | XX.XX | XX.XX to XX.XX | X.XXX | XX.XX | XX.XX to XX.XX | X.XXX |
|  | Total symptom | XX.XX | XX.XX to XX.XX | X.XXX | XX.XX | XX.XX to XX.XX | X.XXX |
|  | Self-efficacy | XX.XX | XX.XX to XX.XX | X.XXX | XX.XX | XX.XX to XX.XX | X.XXX |
|  | Quality of life | XX.XX | XX.XX to XX.XX | X.XXX | XX.XX | XX.XX to XX.XX | X.XXX |
|  | Social limitation | XX.XX | XX.XX to XX.XX | X.XXX | XX.XX | XX.XX to XX.XX | X.XXX |
|  | Overall summary | XX.XX | XX.XX to XX.XX | X.XXX | XX.XX | XX.XX to XX.XX | X.XXX |
|  | Clinical summary | XX.XX | XX.XX to XX.XX | X.XXX | XX.XX | XX.XX to XX.XX | X.XXX |
|  | Total | XX.XX | XX.XX to XX.XX | X.XXX | XX.XX | XX.XX to XX.XX | X.XXX |

✝ Difference calculated with the UCP group as the reference.

| **Table 7b.** Quality of Life Endpoints at 1 year. (ITT population) | | | | | | | |
| --- | --- | --- | --- | --- | --- | --- | --- |
| **Outcome** | | **Adjusted for Site, Device type and Baseline score** | | | **Adjusted for Site, Device type, Age, Gender, NYHC and Baseline score** | | |
|  |  | **Difference^✝^** | **95% CI** | **P value** | **Difference^✝^** | **95% CI** | **P value** |
| **EQ-5D** | Visual Analogue | XX.XX | XX.XX to XX.XX | X.XXX | XX.XX | XX.XX to XX.XX | X.XXX |
|  | Total | XX.XX | XX.XX to XX.XX | X.XXX | XX.XX | XX.XX to XX.XX | X.XXX |
| **SF-12** | Physical Component Summary (PCS) | XX.XX | XX.XX to XX.XX | X.XXX | XX.XX | XX.XX to XX.XX | X.XXX |
|  | Mental Component Summary (MCS) | XX.XX | XX.XX to XX.XX | X.XXX | XX.XX | XX.XX to XX.XX | X.XXX |
|  | Total | XX.XX | XX.XX to XX.XX | X.XXX | XX.XX | XX.XX to XX.XX | X.XXX |
| **KCCQ** | Physical Limitation | XX.XX | XX.XX to XX.XX | X.XXX | XX.XX | XX.XX to XX.XX | X.XXX |
|  | Symptom Frequency | XX.XX | XX.XX to XX.XX | X.XXX | XX.XX | XX.XX to XX.XX | X.XXX |
|  | Symptom burden | XX.XX | XX.XX to XX.XX | X.XXX | XX.XX | XX.XX to XX.XX | X.XXX |
|  | Total symptom | XX.XX | XX.XX to XX.XX | X.XXX | XX.XX | XX.XX to XX.XX | X.XXX |
|  | Self-efficacy | XX.XX | XX.XX to XX.XX | X.XXX | XX.XX | XX.XX to XX.XX | X.XXX |
|  | Quality of life | XX.XX | XX.XX to XX.XX | X.XXX | XX.XX | XX.XX to XX.XX | X.XXX |
|  | Social limitation | XX.XX | XX.XX to XX.XX | X.XXX | XX.XX | XX.XX to XX.XX | X.XXX |
|  | Overall summary | XX.XX | XX.XX to XX.XX | X.XXX | XX.XX | XX.XX to XX.XX | X.XXX |
|  | Clinical summary | XX.XX | XX.XX to XX.XX | X.XXX | XX.XX | XX.XX to XX.XX | X.XXX |
|  | Total | XX.XX | XX.XX to XX.XX | X.XXX | XX.XX | XX.XX to XX.XX | X.XXX |

✝ Difference calculated with the UCP group as the reference.

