***Statistical analysis:***

Cox proportional hazards regression will be used to analyse the primary outcome data according to the intention to treat. The stratifying variables will be entered as covariates and any clinically important baseline imbalance will also be accommodated in the model. Estimates will be reported as hazard ratios with 95% confidence intervals. Secondary clinical outcomes with time to event will be analysed in a similar way using a multifactorial survival analysis modelling method appropriate to the multicentre nature of the data (i.e. to allow for centre effects).

We will censor at time at study end for those alive and free of hospitalisation and at last date known to be free of hospitalisation for those who are lost to follow-up (e.g. leave the area). Withdrawals from RM will be recorded but such will be analysed at ITT.

Quality of life outcomes will be analysed at 1 and at 2 years.

From Euroqol : utility, VAS.

From SF12: Utility; Mental component score (MCS); Physical component score (PCS)

Kansas Heart failure numerical score.

Results will be analysed by multiple or logistic (if pre-specified categories) regression. Multiple imputation will be used to explore the impact of missing data in QoL data.

Cumulative number of unplanned CV hospitalisations will be analysed by multinomial logistic regression

A priori sub group analysis for the primary outcome will be conducted on the following variables:

Age

History of atrial fibrillation

Type of device (ICD, CRT-P,CRT –D)

Baseline functional status (NYHA grade, Kansas HF score).

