### 3.2.2 Secondary Endpoints

The secondary endpoints of the trial are:

1. Time to death.
2. Time to a cardiovascular related death.
3. Time to a non-cardiovascular related death.
4. Time to first unplanned hospitalisation for cardiovascular reasons or cardiovascular related death.
5. Time to first unplanned hospitalisation for non-cardiovascular reasons or death by any cause.
6. Time to first unplanned hospitalisation for cardiovascular reasons.
7. Time to first unplanned hospitalisation for non-cardiovascular reasons.
8. Total number of unplanned hospitalisations.
9. Total number of unplanned hospitalisations for cardiovascular reasons.
10. Change from baseline in SF12 scores at 2 years (physical and mental health components).
11. Change from baseline in EQ5D scores at 2 years.
12. Change from baseline in KCCQ at 2 years.
13. Change from baseline in SF12 scores at 1 year (physical and mental health components).
14. Change from baseline in EQ5D scores at 1 year.
15. Change from baseline in KCCQ at 1 year.
16. Number and cost of hospitalisations.
17. Difference in cost of resources consumed.
18. Difference in cost of cardiovascular related health care use.
19. Incremental costs per quality-adjusted life years (QALYs).

Unless otherwise stated, secondary endpoints will be measured at the last follow-up or at the last available observation within the two year follow-up period.

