## 3.6 Secondary Analyses

Secondary clinical outcomes that are Time to Event will be analysed in a similar way to the primary endpoint. The analyses will be performed on adjudicated events in the ITT population. Subjects who are alive and event free at the end of the trial will be censored at the date of trial completion. Subjects who die (for a non-mortality endpoint) or who die for a different cause than the endpoint under investigation will be censored at their date of death. Those lost to follow-up will be censored at the date that their status was last known.

The total number of unplanned hospitalisations (for cardiovascular reasons and for all reasons) will be analysed using the Andersen-Gill model, a Cox regression model for counting processes. We will also explore the use of Poisson regression (with duration of follow-up included as an offset) and negative binomial models, depending on the range of counts that are seen in the data.

Continuous endpoints will be analysed using Analysis of Covariance (ANCOVA) including the baseline value as a covariate where available. Variables that appear to be skewed following a visual inspection of the separate group histograms will undergo a two parameter Box-Cox transformation prior to analysis.

Analysis approaches for the Health Economics endpoints are discussed in the Health Economics section (Section 4).

All secondary endpoint comparisons will be performed using the ITT population, and will include the same covariates as the model for the primary analysis (site and device type) and will be conducted using a 5% significance level. All estimates will be presented with 95% confidence intervals. There will be no imputation of missing values or adjustment of the significance level for multiplicity.

Time to event comparisons will be visualised using Kaplan-Meier curves.

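### Total unplanned hospitalisations (secondary endpoints 8 and 9): text, table shell and protocol name three different models, no patient-level robust variance is stated, and Table 6 has a mortality row where the CV count should be

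*Combined protocol and SAP*

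**What the plan says.** SAP 3.2.2 lists two count endpoints: number 8, "Total number of unplanned hospitalisations", and number 9, "Total number of unplanned hospitalisations for cardiovascular reasons".

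The methods for them differ by place:

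- **SAP 3.6, main model.** The totals for CV reasons and for all reasons "will be analysed using the Andersen-Gill model, a Cox regression model for counting processes". No robust (sandwich) variance, frailty term or patient cluster is stated, here or elsewhere.
- **SAP 3.6, further models.** "We will also explore the use of Poisson regression (with duration of follow-up included as an offset") is the first. The second is "negative binomial models, depending on the range of counts that are seen in the data".
- **SAP 7.4, Table 6 shell.** The heading is "Poisson regression models for secondary count outcomes (follow-up time included as an offset"). There are two rows: total unplanned hospitalisations, and all-cause mortality. Endpoint 9 has no row, and no other outcome shell carries it.
- **SAP 6.1.2, table list.** Table 6 is described as relative risks for the number of hospitalisations. Mortality is not mentioned.
- **Protocol section 10, Statistical analysis.** "Cumulative number of unplanned CV hospitalisations will be analysed by multinomial logistic regression", with the categories 0, 1, 2 and more than 2 given in the list of endpoints.

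**The concern.** Admissions in heart failure usually cluster: a few patients account for many of them. A plain Poisson model, or an Andersen-Gill model with its model-based variance, treats a patient's admissions as independent given the covariates. If patients differ in underlying rate, the standard error is too small and the test rejects too often, whether the apparent effect is benefit or harm. Reducing admissions is a central aim of the intervention, and any unplanned hospitalisation is also a harm outcome in the protocol. SAP 3.6 tests secondary endpoints at 5% without multiplicity adjustment.

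With three methods named and no stated order between text and table, the result reported for these endpoints could depend on a choice made after the data are seen. Table 6 is also to be repeated for 11 subgroups and for the per-protocol population (SAP 6.1.2), so a defect in the shell would be copied 12 more times.

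**Working it through.** The documents give no event rate, dispersion or power for endpoints 8 and 9, so there is no stated figure to reproduce. The size has to be worked out from an assumption.

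**Inputs**

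- 825 patients per arm; follow-up at least 2 years (SAP 1.2.2).
- Inpatient admissions per patient-year: mean 0.32, 95% CI 0.25 to 0.39, N = 391 (protocol Appendix I). This is the only source of dispersion in the documents. Appendix I says it is a non-ICD population from 2003/4 of uncertain representativeness.
- Longest follow-up about 46 months, or 3.83 years, if the protocol timetable is read as recruitment in months 2 to 24 and follow-up to month 48.

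**Step 1: dispersion from Appendix I**

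- SD = (0.07 / 1.96) × √391 = 0.706, so the variance is 0.499.
- Variance / mean over one year = 0.499 / 0.32 = 1.56. Poisson would give 1.
- Gamma variance k = (0.499 − 0.32) / 0.32² ≈ 1.75.

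**Step 2: effect on a model-based Poisson analysis over 2 years**

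- Variance / mean = 1 + k × 0.32 × 2 = 1 + 1.75 × 0.64 = 2.12.
- Standard error factor = √2.12 ≈ 1.46.
- True size of a nominal 5% test = 2 × [1 − Φ(1.96 / 1.46)] ≈ 17.8%.

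Simulated null trials with 825 per arm agree: 17.5% with the model-based variance and 5.1% with a robust variance (8,000 runs), and 5.0% with a negative binomial model (200 runs).

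**Step 3: range**

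- Rounding of the mean and interval in Appendix I gives a 2-year factor of 1.28 to 1.62 and a size of 13% to 23%.
- Other dispersions (assumed):

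| Gamma variance | Exactly 2 years, by formula: SE factor, size | Follow-up uniform over 2 to 3.83 years, simulated Poisson: size |
| --- | --- | --- |
| 0.5 | √1.32 = 1.15, about 9% | 10.6% |
| 1 | √1.64 = 1.28, about 13% | 15.8% |
| 2 | √2.28 = 1.51, about 19% | 25.2% |

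- With no overdispersion the model-based Poisson test keeps its level (5.2% simulated).

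**Step 4: does it carry over to Andersen-Gill?**

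Yes, if the model-based variance is used. In 2,000 simulated null trials per setting, 825 per arm, rejection was 9.6%, 16.0%, 23.7% and 24.6% at gamma variances of 0.5, 1, 1.75 and 2. With a patient-level sandwich variance it was 4% to 6%. With no heterogeneity the model-based test rejected in 4.5%.

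**Step 5: Table 6 against the endpoint list**

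Endpoint 8 has a row, under Poisson. Endpoint 9 has none. All-cause mortality is not a repeat count, has its own row in Table 5, and does not fit the description of Table 6 in SAP 6.1.2. The main model of SAP 3.6 has no shell of its own.

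**The case against.** The best defence is that the plan is incomplete here rather than wrong, and much of it stands.

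- A reader might infer that clustering is ignored altogether. SAP 3.6 does not support that: it names negative binomial models, which allow for differences between patients. But they are exploratory, their use depends on the range of counts and not on a dispersion criterion, and they do not appear in Table 6.
- A reader might infer that the intervals will be too narrow. The SAP does not say which variance Andersen-Gill will use, and it does not exclude a robust one. The inflation is conditional on a model-based variance and on overdispersion.
- A reader might infer that the CV count will go unreported. SAP 3.6 commits to analysing "The total number of unplanned hospitalisations (for cardiovascular reasons and for all reasons"), and Section 6 allows tables to change and be added. The mortality row looks like a drafting slip in a shell.
- A reader might carry the point over to cost-effectiveness. SAP Section 4 works with patient-level costs and QALYs and bootstraps them jointly, so it does not use these standard errors.
- SAP 3.2.2 may limit secondary endpoints to two years (its wording is ambiguous). That favours the lower figures, but the size at 2 years is still about 18% with the Appendix I dispersion.
- The SAP is meant to specify the final analysis further, so its methods can be taken to supersede the multinomial model. It does not say that they do.

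The latitude over tables does not settle which model is the main one or which variance it uses. That part of the concern survives.

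**Conclusion.** The point holds in this form. For endpoints 8 and 9 the SAP text, the SAP table shell and the protocol name three different methods; no patient-level robust variance is stated for Andersen-Gill or Poisson; and Table 6 carries a duplicated mortality row in place of endpoint 9. These are plain from the documents.

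The statistical consequence is conditional. If model-based variances are used, and if dispersion is as Appendix I implies, Poisson standard errors are too small by a factor of about 1.46 over 2 years and a nominal 5% test has a true size of about 18%. Across gamma variances of 0.5 to 2 and follow-up from exactly 2 years to a spread of 2 to 3.8 years, the size runs from about 9% to 25%. A sandwich variance brings it back to about 5%. The dispersion comes from patients without ICDs and may not match the trial's.

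This should be fixed, but it is not critical: two of 19 secondary endpoints are affected, and the primary Cox analysis is untouched.

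**What to change.** 1. In SAP 3.6, pre-specify one main model for endpoints 8 and 9: either Andersen-Gill with a patient-level sandwich variance, or negative binomial with log follow-up time as offset. Label any other model as a sensitivity analysis, and drop the choice based on the counts seen.
2. Retitle Table 6 to match that model.
3. Replace its all-cause mortality row with "Total number of unplanned hospitalisations for cardiovascular reasons".
4. Record that the chosen model replaces the protocol's multinomial logistic regression.

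A joint frailty model for admissions and death is optional as a sensitivity analysis.

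The cost is a few lines of SAP text, one corrected table shell and one option in the model call; no new data are needed. The downside is wider intervals wherever admissions are overdispersed.

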## 7.5 Trial Timeline

## 7.6 Health economics: questionnaire and results (RMS)

### 7.6.1 Questionnaire sent to RMS

Please estimate the average number of hours per week the remote monitor role at your site is spending in each of the following three activity groups, both during the first year if you were employed at that time and again now. Please put a whole number in here not a range. It is just your estimate.

| **Site name:** | **Year 1** | **Year 3** |
| --- | --- | --- |
| **Download specific:**  *Reviewing the downloads*  *Initiating interventions as a result of the downloads* |  |  |
| **Research Specific Activity:**  *Screening patients*  *Randomisation and baseline visits*  *Research paperwork- GP information sheets, health questionnaires*  *ECRF data entry*  *Reporting SAEs and collecting source data*  *Follow up visits* |  |  |
| **Other:**  Any other activity or tasks such as other duties/mandatory training /meetings etc |  |  |

Thank you for completing this.

### 7.6.2 Results of RMS survey

| Year 1 | Newcastle | Guys | Liverpool | Blackpool | Leicester | Leeds | Soothampton | Brompton | Manchester |  |  |
| --- | --- | --- | --- | --- | --- | --- | --- | --- | --- | --- | --- |
| Monitoring | 18 | - | 12 | 14 | 10 | 12 | 6 | 10 | - | 12 | 31 |
| Research | 18 | - | 25 | 20 | 28 | 35 | 25 | 12 | - | 23 |  |
| Other | 2 | - | 1 | 3 | 5 | 2 | 4 | 1 | - | 2 |  |
| total | 38 |  | 38 | 37 | 43 | 48 | 35 | 23 |  | 37 |  |
| Year 2 |  |  |  |  |  |  |  |  |  |  |  |
| Monitoring | 12 | 22 | 10 | 10 | 15 | 17 | 12 | 6 | 10 | 13 | 39 |
| Research | 18 | 15 | 27 | 22 | 21 | 16 | 20 | 5 | 15 | 18 |  |
| Other | 2 | 1 | 1 | 5 | 2 | 1 | 4 | 1 | 3 | 2 |  |
| total | 32 | 38 | 38 | 37 | 38 | 33 | 36 | 12 | 28 | 32 | 39 |

Of the 9 centres, 7 replied for year one, and all in year two. These replies put the mean number of hours in year one at 37, with 12 devoted to monitoring. Figures for year two were 32 and 13 hours per week, respectively.

For costing, the mean number of hours per week in each centre devoted to monitoring will be 12 in year one and 13 in year two.

